#### Mobility in life-space

Mobility in life space will be a secondary outcome of the study and will be assessed by the LSA, which allows the characterization of mobility in life-spaces (other rooms of your home besides the room where you sleep; to an area outside your home, places outside your neighborhood but within your town; and to places outside your town), specifically frequency, need for mobility aids and the help of third party in the last 4 weeks [14]. Four indicators are calculated (with the highest scores indicating greater life space):

Independent life-space: the highest life-space level attained without help from a person or mobility aid.Life-space using equipment: the highest life-space level attained when a mobility aid was used, without help from a person.Maximal life-space: the highest life-space level attained with the help of a person or mobility aid.Composite score: encompasses distance, frequency, and level of independence, with a range from 0 to 120.

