### Outcomes

#### Primary outcome

The primary outcome will be fear of falling.

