### Statistical analysis

Continuous variables will be expressed on average and standard deviation or median and interquartile interval 25%-75%. Categorical data will be presented in absolute and relative numbers. To verify the distribution normality of data, the Shapiro-Wilk normality test will be applied. For comparisons between groups over time, One-way ANOVA test for parametric data or Kruskall-Wallis for non-parametric data will be used. For intragroup analyses, repeated measures Analysis of Variance (RM-ANOVA) test for parametric data or Friedman test for non-parametric data will be used. Only for the Time Up and Go variable before and after intervention, a paired t-test will be used for parametric data, or a Wilcoxon test will be used for non-parametric data. For intergroup and intragroup analyses, the baseline, 3 and 6 months after discharge from the geriatric ED will be considered. To evaluate correlations, the Pearson correlation test will be used for parametric data and the Spearman test will be used for non-parametric data. All the analyses will be carried out using the Statistical Package for Social Sciences (SPSS) version 28.0.1 (SPSS Inc.^®^; Chicago, IL, USA), considering a significance level of 5%.

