Telemonitoring has been more frequently studied in older adults, but mainly in ambulatory settings and focused on chronic illnesses [48–50]. In this study, the intervention will be evaluated in acutely ill older patients admitted to a Geriatric ED and trained in the use of walking aids. In addition, in a randomized clinical trial, telemonitoring could be an additional strategy to reduce the loss of follow-up of participants during the study.

Finally, to the best of our knowledge, there are no previous studies that have compared groups according to the provision of gait assistance devices and used FES-I as a main outcomes. Therefore, we’ve calculated the sample size using as a reference the study by Morgan et al. [11] which proposed a gait assistance device intervention in its participants and had a higher reported DMC than other initiative [51] but conducted intragroup comparisons. In addition, our study will also address intragroup differences when comparing baseline, 3 and 6 months after discharge from the geriatric ED.

A limitation of the study protocol is that it will be performed in a single center. However, having been described in detail, registered in a public database, and published in an open-source journal, it might be replicated by other research groups around the globe. In addition, another limitation of the study is that participants in the control group may initiate the use of assistive gait devices over the 6-month study period. However, this identification will be possible through the LSA questionnaire. After completion of the study and blind analysis of the data by the statistician, the percentage of individuals in the control group who initiated the use of gait devices will be shown. If there are patients in the control group who initiated the use of a gait device, it will be considered a protocol deviation from the assessment point at which they started using the assistive gait device, which may be 3 or 6 months after discharge from the geriatric ED service. Consequently, a secondary analysis will be presented without the protocol deviation values.

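### The secondary analysis that drops control values after device uptake, with no matching rule for the walking-aid arms, compares a selected control group with unselected ones

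*Protocol article*

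**What the plan says.** The rule stands in the limitations paragraph of the Discussion in the protocol article. The sponsor recognises that "participants in the control group may initiate the use of assistive gait devices over the 6-month study period". On detection it says "However, this identification will be possible through the LSA questionnaire", and it promises to report the percentage of controls who took up a device. The rule itself is: "If there are patients in the control group who initiated the use of a gait device, it will be considered a protocol deviation". It applies "from the assessment point at which they started using the assistive gait device, which may be 3 or 6 months after discharge", and the consequence is: "Consequently, a secondary analysis will be presented without the protocol deviation values".

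Four other places bear on it:

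- Mobility in life-space: the LSA records movement, "specifically frequency, need for mobility aids and the help of third party in the last 4 weeks".
- Assessment moments: the LSA is repeated at 3 and 6 months, with no restriction to one arm.
- Primary outcome: "The primary outcome will be fear of falling", measured by the FES-I, on which higher scores mean more concern.
- Statistical analysis: "For comparisons between groups over time, One-way ANOVA test for parametric data or Kruskall-Wallis for non-parametric data will be used". No covariate adjustment is described there, and the deletion analysis is not mentioned.

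No deviation is defined for a WA or WAT participant who never uses the aid or gives it up.

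**The concern.** Randomisation makes the three arms comparable in everything that precedes treatment. Removing values according to what a participant does later, in one arm only, gives that protection up. The control values that stay come from people who did not start a device; the values in the other two arms come from everyone followed up, users and non-users alike as far as the text goes.

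The deletion would be harmless only if starting a device had nothing to do with fear of falling, and the protocol's own content makes that doubtful. Under Sample, every participant, controls included, enters with at least one indication for a mobility aid, and a recent fall is one of the listed indications. The Introduction hypothesises that fear of falling goes with poorer mobility and with fall risk, and these are plausible reasons for acquiring an aid.

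At stake is what can be learned about contamination of the control arm. An analysis meant to show the picture without contamination may be off by an unknown amount in an unknown direction.

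**Working it through.** **Inputs from the protocol (Sample).** SD of FES-I 12; planning difference 8.2 points. The article gives no figure for uptake or for its relation to FES-I, so there is no planned value to reproduce.

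**Assumptions, not in the documents.** A proportion p = 10–30% of controls start a device. The tendency to start has correlation ρ = 0.2–0.5 with the FES-I score the person would have without a device. Both are taken as normally distributed.

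**Step 1: shift from the deletion, no true effect.** If the fraction p with the highest tendency to start is removed, the mean of the remaining controls falls by

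shift = ρ × 12 × φ(z) / (1 − p), where z is the (1 − p) standard normal quantile and φ the normal density.

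- p = 10%: z = 1.282, φ = 0.1755; 12 × 0.1755 / 0.9 = 2.34
- p = 20%: z = 0.842, φ = 0.2800; 12 × 0.2800 / 0.8 = 4.20
- p = 30%: z = 0.524, φ = 0.3477; 12 × 0.3477 / 0.7 = 5.96

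Multiplying by ρ, with the percentage of 8.2 in brackets:

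| Uptake | ρ = 0.2 | ρ = 0.3 | ρ = 0.5 |
|---|---|---|---|
| 10% | 0.47 (6%) | 0.70 (9%) | 1.17 (14%) |
| 20% | 0.84 (10%) | 1.26 (15%) | 2.10 (26%) |
| 30% | 1.19 (15%) | 1.79 (22%) | 2.98 (36%) |

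A simulation with 1,000,000 per arm agrees: 0.71, 1.30 and 1.78 at ρ = 0.3; 1.15, 2.12 and 3.00 at ρ = 0.5. Keeping all controls gives a difference of about 0.0 throughout.

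**Step 2: direction.** With positive ρ (more fearful controls start) the control mean drops, WA minus control moves upward, and a benefit is masked. With negative ρ the sign flips: at ρ = −0.3 and p = 30% the shift is −1.79. With ρ = 0 there is none.

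**Step 3: test level.** Three-group ANOVA, no true effect, 42 per arm before deletion (the article's 42 read as a per-group figure, since 42 × 1.2 = 50.4, rounded up to 51), 8,000 runs. Rejection rates at nominal 5% for p = 10, 20, 30% were 5.2, 7.2 and 8.6% at ρ = 0.3, and 6.8, 10.0 and 16.3% at ρ = 0.5. The simulation standard error near 5% is √(0.05 × 0.95 / 8,000) = 0.24 percentage points, so 5.2% is indistinguishable from nominal.

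**Step 4: does the deletion recover the effect of the device?** Suppose the aid lowers FES-I by 8.2 in everyone who uses it, all WA participants use it, and 30% of controls start one and gain the same.

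- All values as allocated: −8.2 × (1 − 0.3) = −5.74
- Control-only deletion, ρ = 0: −8.2
- ρ = 0.3: −8.2 + 1.79 = −6.41
- ρ = 0.5: −8.2 + 2.98 = −5.22
- ρ = −0.3: −8.2 − 1.79 = −9.99

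The deletion returns −8.2 only when uptake is unrelated to prognosis. At ρ = 0.5 it lies further from −8.2 than the as-allocated figure does. A complier-average estimate divides the as-allocated difference by the difference in device use: −5.74 / (1 − 0.3) = −8.2, whatever ρ is, provided allocation acts only through device use.

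**The case against.** **It is only a secondary analysis.** This stands. The text calls it secondary, which implies that the main comparison keeps these values; no sample size or decision rule rests on the deletion. A reader might infer that the primary result is compromised. The documents do not support that.

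**Values are removed, not people.** This stands. A control who starts at 6 months keeps the baseline and 3-month values. A reader might infer that whole participants are excluded; the rule does not say so. The shift at the affected visit is the same.

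**Reporting the uptake percentage already informs the reader.** This stands in part. The deletion is not the only response to contamination, and uptake in controls will be visible. But a percentage does not tell the reader how far the selection has moved the estimate.

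**The asymmetry rests partly on silence.** The article does not say in words that WA and WAT non-users stay in this analysis, and adherence definitions may sit in a fuller plan. That is fair, but the deviation rule as published names one arm and no other.

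**The size is assumed.** This stands. The low corner is 6% of the planning difference. With 42 per arm the standard error of a two-arm difference is 12 × √(2/42) = 2.6 points, so all but the largest shift in the table lie inside one standard error.

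**A false benefit?** A reader might infer that the deletion would manufacture one. Under the likelier mechanism, more fearful controls starting, it works against the aid. Exaggerating a benefit needs the opposite selection, for which the documents give no argument.

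**A complier estimate has its own assumptions.** This also stands, and it limits the choice of comparison. Under Telemonitoring, the fortnightly WAT calls reinforce safe-gait guidance as well as device use, so they may change fear of falling by another route. Pooling WA and WAT as one instrument is therefore unsound.

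**Conclusion.** The concern holds for the secondary analysis and no further. As published, the rule conditions on post-randomisation behaviour in the control arm alone, and it is biased unless starting a device is unrelated to FES-I. Under the assumed 10–30% uptake, correlation 0.2–0.5 and SD 12, the shift is about 0.5 to 3.0 points (6–36% of 8.2). These figures illustrate and do not forecast. The direction is not fixed: a benefit is masked if more fearful controls start, and exaggerated if less fearful controls do. Nothing in the article gives this analysis priority or presents it as the true effect. The risk is that readers treat it as the uncontaminated result when it is that only under an assumption the protocol does not state.

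**What to change.** 1. State that conclusions rest on the comparison of all randomised participants in their allocated arms, with all available values kept whatever device is used. This makes explicit what the wording already implies.
2. Replace the control-only deletion with an analysis that uses LSA-recorded device use in every arm. A suitable choice is a complier-average estimate for WA versus control, with allocation as the instrument, adjusted for baseline FES-I. Do not pool WA with WAT.
3. State its assumptions: training affects fear of falling only through device use, and exposure is known only for the four weeks the LSA covers before each assessment, so some misclassification must be expected.
4. Report device use at 3 and 6 months in all three arms, not in controls alone.
5. If the deletion analysis is kept, label it exploratory, state its likely selection bias, and draw no efficacy conclusion from it.

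The cost is a short passage of text and a little more analysis work. The LSA is already repeated at both follow-up assessments, so no new data collection is needed. The complier-average estimate will have a wider confidence interval than the as-allocated one.
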